### Procedure

Once potential participants are recruited by the physical therapy association team, the research team will provide them with detailed information about the study’s objectives. Individuals who potentially meet the inclusion and exclusion criteria will be preselected for participation. Participants who agree to participate will be asked to provide written informed consent. A trained researcher with expertise in neurological assessment will schedule each enrolled participant for the baseline evaluation. All assessments will be conducted by the same evaluator and in the same facility at the Parkinson’s Association of Aragón to ensure consistency in testing conditions. Each evaluation session will last approximately 60 minutes.

After the initial assessments, participants will be randomly assigned to either the experimental or control group. Participants will be instructed not to disclose their group assignment to the evaluator during follow-up assessments to minimize potential bias. Intervention in both groups will be administered by 3 physical therapists, each with at least 2 years of experience managing patients with neurological conditions. To ensure consistency and adherence to the study protocol, all therapists will attend a training session focused on standardizing the intervention procedures. Additionally, they will be provided with detailed written guidelines for the intervention. This process will be implemented to ensure consistent patient management across physical therapists and to facilitate accurate documentation of any adverse events that may occur during the intervention.

### Intervention

A total of 8 face-to-face physical therapy sessions will be conducted over a 4-week period, with a frequency of 2 sessions per week and a follow-up 3 months after the intervention. Each session will last 40 minutes, divided into 2 separate 20-minute segments.

The first part of the intervention will be the same for both groups and will consist of a usual physical therapy session based on the Modified Fitness Counts (mFC) exercise program [33], during which participants will perform 15 repetitions of eccentric exercises targeting antigravity muscle groups, including the trunk, knee flexors and extensors, and hip extensors. Exercises will be performed either in a sitting or standing position, depending on the specific muscle group involved. Movements will be executed at a slow contraction velocity to minimize compensatory strategies. The duration of the eccentric phase will be a maximum of 3 seconds and 1 second for the isometric hold [34].

The second part of the treatment protocol will differ according to group allocation. In the experimental group, the second part of the intervention will consist of a personalized static and dynamic balance physical therapy program delivered through IVR using the Oculus Quest 2 VR headset and FisioVR^®^ software (Abaco Digital, Zaragoza, Spain). This program includes a series of 360º spherical images depicting urban environments familiar to the participants, designed to simulate realistic scenarios in which various postural activities are performed. The immersive setting allows participants to move and explore the virtual environment with greater freedom, engaging in both static and dynamic balance mechanisms. Throughout the intervention, the physical therapist will continuously monitor on a computer the exact content the patient is viewing in the VR environment.

At the beginning of each session, participants will be seated comfortably while the VR headset is fitted and adjusted to ensure optimal focus and comfort. A brief familiarization phase will follow, during which participants will identify objects and landmarks within the environment to confirm adequate visual clarity. Throughout this initial phase, subjective feedback regarding visual distortion, discomfort, or disorientation will be collected to monitor adaptation to the immersive environment. This phase will last 3 minutes [35].

The intervention will include 4 distinct virtual scenarios, each designed to challenge different types of balance (static or dynamic) and stability tasks. Depending on task demands, balance can be classified as quiet (in a stable environment), reactive (in response to unexpected perturbations), or proactive (in anticipation of destabilizing forces) [17].

Participants will complete dual tasks, combining balance maintenance with simultaneous motor and/or cognitive challenges (e.g., mental counting, working memory tasks, or internal arithmetic calculations). In each of the 8 sessions, participants will encounter 4 scenarios, each with different exercises. Each exercise will be structured into 4 difficulty levels: Beginner (Level 1), Easy (Level 2), Intermediate (Level 3), and Advanced (Level 4). For each exercise, participants will begin at the Beginner level. Performance will be assessed based on balance. If the exercise is completed with no more than one loss of balance, participants will progress sequentially to the next difficulty level (Easy, Intermediate, and Advanced). This stepwise progression will continue until the highest difficulty level that can be safely performed is reached. In each scenario, participants will perform the exercises at the highest difficulty level achieved according to this criterion. The exercises are shown in Table 1.

**Table 1 pone.0344457.t001:** Experimental group. Balance physical therapy program using IVR.

ENVIRONMENTS		PROGRESSION LEVELS				DUAL TASK
		BEGINNER	EASY	INTERMEDIATE	ADVANCED	
**Environment 1.**		Walk around the stage.	Move around the stage by taking a stride.	Move around the stage walking in a semi-tandem gait.	Move around the stage walking in a tandem gait.	Questions will be asked such as: - Look across and tell me what you see. - What shape is the building? - What color is the building? - What book is there on the lectern?
**Environment 2.**	**Static balance.**	Two-point support, following with eyes and head.	Tandem supports different feet and tracking with eyes and head.	Monopodial support with different feet and tracking with eyes and head.	Monopodial support tracking with eyes and head on unstable surface.	Questions will be asked such as: - Look across and tell me what you see. - What color is the dot? - What color is the wall? - You can point out where the dot is? - Do you hear anything? What?
	**Dynamic balance.**	Walk following the dot, with their normal gait.	Walk following the dot with a striding gait.	Walk following the dot with a semi-tandem gait.	Walk following the dot with a tandem of gait.	
**Environment 3.**	**Static balance.**	With your feet shoulder-width apart, stand still and try to dodge the balls.	With your feet on the ramp, stand still and try to dodge the balls.	With your feet in tandem, stand still and try to dodge the balls.	With your feet in tandem and on an unstable surface, stand still and try to dodge the balls.	Questions will be asked such as: - What color is the ball? - What kind of ball does it remind you of? - Is that ball used in any sport? - Is there anything else around? - How many balls have come toward you? - How many balls were red? - Do you hear anything? What?
	**Dynamic balance.**	Hit the balls with your hands alternately. 5 times with each hand.	Hit the balls with your feet alternately. 5 times with each foot.	Hit the balls with your hands or feet alternately. 5 times with each of the 4 limbs.	Hit the balls with your hands or feet alternately on an unstable surface.	
**Environment 4.**		Stay in your position and only dodge people by stepping to the right or left.	Walk, and when you meet someone, avoid them.	Walk with long strides and when you meet someone, avoid them.	Walk in tandem on a line and when you meet someone, avoid them.	Questions will be asked such as: - Does this tunnel seem very dark? Does the light bother you? - Does it change your vision at all? - How many people have you crossed paths with? How many women have you seen? And men? - What color was the first person’s shirt? And the last person’s pants? - Where are you walking? Describe everything you see. - Describe the girl. Describe the boy.

Participants in the control group will follow a static and dynamic balance program based on usual physical therapy balance exercises [36]. The specific balance exercise program and its progression will be adapted to each participant’s individual condition. As in the experimental group, the usual balance exercises will be structured into 4 progressive levels of difficulty, from Beginner (Level 1) to Advanced (Level 4), with specific exercises adapted to each level. Participants will perform the exercises at the highest possible level of difficulty, which will be assessed by measuring the loss of balance. Participants should not experience more than one loss of balance before progressing to a higher level of difficulty. These exercises are listed in Table 2.

**Table 2 pone.0344457.t002:** Control group. Usual physical therapy balance exercise program.

				PROGRESSION LEVEL			
EXERCISE	BALANCE COMPONENT	PROGRESSION PRINCIPLE	DESCRIPTION	BEGINNER	EASY	INTERMEDIATE	ADVANCED
**Exercise 1. Posture**	Static balance	Increase challenge via eyes closed, unstable surface	Place both feet aligned with a separation of 5 cm. Look at a fixed point in front of you. You must maintain this posture without moving for 30 seconds.	Two-foot balance on a stable surface with eyes open.	Two-foot balance on a stable surface with eyes closed	Two-foot balance on an unstable surface with eyes open.	Two-foot balance on unstable surface with eyes closed.
**Exercise 2. Tandem/Semi-tandem**	Static balance	Increase base of support complexity and sensory challenge	**Semi-tandem:** Place your right heel in front of the sides of your left foot. Hold this position for 30 seconds. Now place your left foot in front and repeat the exercise. Repeat each side as many times as necessary until you change levels. **Tandem**: Place your right heel in front, touching the toes of your left foot. Hold this position for 30 seconds. Now place your left foot in front and repeat the exercise. Repeat each side as many times as necessary until you change levels.	Semi-tandem position with eyes open.	Semi-tandem position with eyes closed.	Tandem position with eyes open.	Tandem position with eyes closed.
**Exercise 3. Single-leg support**	Static balance	Gradual load on single leg + sensory challenge	Place your hands on your hips, then lift your right leg without resting it on the other leg (single-leg support with the non-supporting leg brought forward). Hold this position for 30 seconds. Repeat with each leg as many times as necessary until you change levels.	Single-leg stance with eyes open.	Single-leg stance with eyes closed.	Single-leg stance with eyes open on an unstable surface.	Single-leg stance with eyes closed on an unstable surface.
**Exercise 4. Inclined ramp**	Static balance	Surface instability + eyes open/closed	Climb onto the inclined ramp with your heels touching the floor. Spread your feet shoulder-width apart. Hold this position for 30 seconds. As a precaution, do this near a wall so that the individual can stabilize themselves if necessary. Repeat as many times as necessary until changing levels.	Inclined ramp with eyes open.	Inclined ramp with eyes closed.	Perform the same exercise with your eyes open on an unstable surface. Place foam rubber on the inclined ramp.	Perform the same exercise with your eyes closed on an unstable surface on the inclined ramp.
**Exercise 5. Compensatory correction step**	Dynamic balance	External perturbation, maintain stability	Remain upright, the physical therapist will place their hands against you, one on each shoulder, and you should lean back onto the physical therapist. When the physical therapist removes their hands, you should maintain your balance by taking a step to keep it. Repeat as many times as necessary until you change levels.	Individual with eyes open.	Individual with eyes closed.	Individual on unstable surface with eyes open.	Individual on unstable surface with eyes open.
**Exercise 6. Semi-tandem and tandem walking**	Dynamic balance	Gait complexity + sensory manipulation	Walking in semi-tandem and tandem positions, the physical therapist will indicate whether you should keep your eyes open or closed. Repeat the exercise as many times as necessary until you reach a new level.	Semi-tandem walking with eyes open.	Semi-tandem walking with eyes closed.	Semi-Tandem walking with eyes open.	Tandem walking with eyes closed.
**Exercise 7. Striding**	Dynamic balance	Increase gait complexity + base of support	Striding. The physical therapist will indicate whether you should keep your eyes open or closed. Repeat the exercise as many times as necessary until you reach a new level.	Striding with eyes open.	Striding with eyes closed.	Striding following a straight line with eyes opened.	Striding following a straight line with eyes closed.
**Exercise 8. Walking with pelvic–shoulder dissociation**	Dynamic balance	Motor-cognitive dual task + gait challenge	Walking with pelvic-shoulder dissociation with two poles (spikes). The physical therapist will give you instructions on whether to do this with your eyes open or closed. Repeat the exercise as many times as necessary until you reach a new level.	Normal walking with two poles that you will move alternately.	Normal walking with two poles that you will move alternately with your eyes closed.	Walk in semi-tandem with two poles, moving them alternately while following a line with your eyes open.	Walk in semi-tandem with two poles, moving them alternately while following a line with your eyes closed.

To ensure participant safety and prevent falls, all intervention sessions will be conducted under continuous one-to-one supervision by an experienced physical therapist. The physical therapist will remain nearby at all times, will monitor task execution, and will provide immediate physical assistance in the event of balance loss.

For participants in the experimental group, the physical therapist will administer the SSQ immediately at the end of each session to monitor potential adverse effects associated with IVR exposure, including nausea, oculomotor discomfort, dizziness, and disorientation. SSQ scores and any reported symptoms will be systematically recorded. If relevant symptoms are detected, the session will be paused, and persistent or severe symptoms will result in discontinuation of the intervention and documentation as adverse events. Any adverse events occurring in the control group will be also monitored and reported during the study.

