**Quality of life**. Health-related quality of life will be measured using the Parkinson’s Disease Questionnaire-39 (PDQ-39). This self-administered instrument consists of 39 items distributed across 8 dimensions and will assess quality of life during the previous month in individuals with PD. Each item is scored on a 5-point ordinal scale ranging from 0 (never) to 4 (always). The scores for each dimension are averaged and transformed to a scale of 0–100, where 0 represents the best possible quality of life and 100 the worst. Lower values will indicate a better perceived quality of life, and higher values will reflect a greater impact of the disease [49]. The PDQ-39 has demonstrated high test-retest reliability [50].

**Adverse symptoms**. Adverse symptoms related to IVR exposure will be monitored using the Simulator Sickness Questionnaire (SSQ). This questionnaire includes 16 items across 3 domains: oculomotor symptoms, nausea, and disorientation. Symptoms will be scored for intensity and interpreted as follows: < 5 = insignificant, 5–10 = minimal, 10–15 = significant, 15–20=concerning, and >20 = severe [51]. This questionnaire will also serve as a criterion for discontinuing participation in the IVR physical therapy program. Participants who score 20 will be withdrawn from the study, as this reflects the presence of severe symptoms identified by the scale. The SSQ has demonstrated good internal consistency [52].

**Satisfaction**. Participant satisfaction with the intervention will be assessed using an *ad hoc* one-question questionnaire developed for this clinical trial. Responses will be recorded on a 5-point Likert scale, where 1 will indicate “very dissatisfied” and 5 will indicate “very satisfied.”

**Adherence**. A participant’s adherence will be evaluated based on attendance records during the intervention phase. Individuals were categorized as showing *high adherence* when they attended no fewer than 80% of the scheduled sessions and completed all prescribed exercises or more. In contrast, *non-adherence* was defined as attending fewer than 20% of the total sessions planned [53].

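### Adverse events are ascertained by different rules in the two arms, so their counts cannot be compared in either direction

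*Protocol article*

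**What the plan says.** The safety paragraphs that follow Table 2 in the Intervention section treat the arms differently.

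- **IVR arm, elicitation.** After each session "the physical therapist will administer the SSQ immediately at the end of each session", and "SSQ scores and any reported symptoms will be systematically recorded".
- **IVR arm, classification.** Relevant symptoms pause the session. Beyond that, "persistent or severe symptoms will result in discontinuation of the intervention and documentation as adverse events".
- **Control arm.** "Any adverse events occurring in the control group will be also monitored and reported during the study". No instrument, definition or severity qualifier is given.

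The Procedure section describes training and written guidelines for the three therapists who treat both groups. One stated purpose is "to facilitate accurate documentation of any adverse events that may occur during the intervention", with no limit by arm or severity.

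Under Secondary outcomes, the adverse-symptoms measure is the SSQ, tied to IVR exposure, with upper bands "10–15 = significant, 15–20=concerning, and >20 = severe". It has no control-arm counterpart.

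**The concern.** The Intervention section gives one condition two jobs in the IVR arm: it ends treatment, and it is the only stated trigger for calling a symptom an adverse event. A symptom that leads only to a pause, or one that passes with an SSQ in the significant or concerning band, is recorded, but nothing there makes it an adverse event. The control sentence has no such filter. On the other side, only IVR participants are questioned with a structured instrument after each session, whereas nothing says how control events come to light.

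Safety matters to this trial's conclusions. The abstract says that showing safety would support wider use of IVR, and the Discussion treats adverse effects as essential to judging acceptability. Because control-arm adverse events are to be reported, a reader of the results will see two counts side by side that were produced by different definitions and different elicitation.

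**Working it through.** The plan gives no figure for adverse events, so there is none to reproduce. The check compares the texts, then asks in which direction the difference could push the counts.

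**1. The rules side by side**

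| | IVR arm | Control arm |
|---|---|---|
| Structured questioning | SSQ after each of 8 sessions | none stated |
| Symptoms recorded | all SSQ scores and any reported symptom | not stated |
| Rule for classing a symptom as an adverse event (Intervention) | persistent or severe | any adverse event, undefined |
| General rule (Procedure) | any adverse event | any adverse event |
| Adverse event window (Intervention) | none stated | during the study |

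Elicitation and classification both differ by arm. The Procedure rule and the IVR rule in the Intervention section are not reconciled.

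**2. Scale**

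- Sample size calculation: 28 participants per group. Intervention: 8 sessions each. 28 × 8 = 224 IVR sessions.
- The only symptom rate in the document is the Discussion's citation of a VR study: at least one adverse symptom in 8.5% of sessions. 224 × 0.085 = 19.0 sessions.
- If 10% to 25% of these were persistent or severe (assumption), 1.9 to 4.8 would be classed as adverse events under the Intervention rule. The remaining 14.2 to 17.1 would appear only as symptom records.

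The Discussion adds that only 20% of the symptoms in that study were directly related to VR. The 8.5% serves here for scale only.

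**3. Direction**

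Assume equal true symptom rates in both arms and complete capture by the SSQ. Let f be the share of IVR symptoms that are persistent or severe, and c the share of control symptoms that come to light without a questionnaire and are counted. Then

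documented ratio, IVR to control = f / c.

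Neither f nor c is in the document, so both are shown as ranges.

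| f | c = 0.1 | c = 0.2 | c = 0.5 | c = 1.0 |
|---|---|---|---|---|
| 0.1 | 1.0 | 0.5 | 0.2 | 0.1 |
| 0.2 | 2.0 | 1.0 | 0.4 | 0.2 |
| 0.5 | 5.0 | 2.5 | 1.0 | 0.5 |
| 0.8 | 8.0 | 4.0 | 1.6 | 0.8 |

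The ratio is below 1 when f < c and above 1 when f > c. If every recorded IVR symptom were counted instead, the ratio would be 1 / c, which is 10 at c = 0.1 and 1.0 at c = 1.0 and never favours IVR. With no true difference, the reported counts could therefore show IVR as safer, equal or worse.

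**The case against.** The strongest reply is that the quoted IVR sentence says what follows persistent or severe symptoms, not that only these are adverse events. It covers symptoms around IVR exposure rather than falls or injuries, and the Procedure section supplies a general rule for both arms. All IVR symptoms are recorded. No between-arm adverse event test is named; the Statistical analysis section has only a generic test for categorical outcomes. Detailed definitions often sit in a full protocol that is not shown.

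Much of this stands, and it rules out several stronger readings that a reader might infer:

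- **That the design favours IVR by construction.** This looks only at the classification rule. Questioning the IVR arm alone pushes the other way, and the table shows that either may dominate. The control threshold is undefined, which is not the same as lower.
- **That the IVR arm has a shorter adverse event window.** The end of each session is when the SSQ is given. No adverse event window is set for the IVR arm, and the control sentence reads as adding controls to monitoring already described.
- **That mild or moderate IVR symptoms would be hidden.** They are recorded at every session and form a listed secondary outcome.
- **That IVR events would be under-counted 4- to 10-fold against controls.** That factor is only the reciprocal of the assumed 10% to 25%, and as a between-arm contrast it needs c = 1, which the document does not support.

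The reply does not remove the mismatch. The article states these rules; they are not simply left to another document. Recording a symptom and documenting it as an adverse event are separate steps in the text, and the recorded IVR symptoms have no control counterpart. Even without a formal test, control-arm events will be reported.

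**Conclusion.** The concern holds as a problem of comparability. The arms differ in how adverse events are elicited and, for symptoms, in the stated rule for counting them, and the Procedure and Intervention sections are not reconciled. The one safety measure collected in both arms therefore cannot support a statement that IVR is as safe as, safer than or less safe than usual balance exercises.

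No net direction or size of bias can be given. Under equal true rates and complete SSQ capture, the ratio in the grid runs from 0.1 to 8.0, depending wholly on two quantities that the document does not supply. The symptom data within the IVR arm are sound for describing IVR tolerability. The point deserves correction because the remedy is small and safety is part of the trial's case for IVR.

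**What to change.** Reconcile the Procedure and Intervention sections as follows.

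1. Use one adverse event definition for both arms: any untoward event or symptom, graded by severity, with duration and action taken.
2. Elicit it with the same open question after every session and at the follow-up visits in both arms.
3. Keep documentation as an adverse event separate from the discontinuation rule, and leave that rule itself unchanged.
4. Report adverse events by arm on the common definition, and report the SSQ as an IVR-only outcome.
5. Recruitment opened in February 2025, so sessions may already have been held. For these, reclassify the recorded IVR symptoms under the common definition before analysis, and state that control-arm events were not elicited in the same way.

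The cost is a wording change and one extra question per session. The reported adverse event count may rise. Step 5 cannot recover control events that were never asked about, so comparability for those earlier sessions stays limited.
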